### **3.4 Duration of the study period for each subject**

The surgical arm of the factorial design will involve an intervention which solely occurs intraoperatively having no impact on perioperative care. The pharmacological arm of the factorial design will involve patient compliance taking a medication from the time of consent (preoperative) to the time of follow-up at 1-year. Study supplements will be held the day of surgery and, following surgery, will commence once the patient is able to take oral medications. Patients will be followed for 1 year post-CABG.

## **4 STUDY POPULATION**

### **4.1 Inclusion Criteria**

- i. Age >18 years
- ii. Able to provide informed consent
- iii. Isolated CABG, non-emergent, on- or off-pump (cardiopulmonary bypass)
- iv. Primary or re-do CABG (if re-do, all previous grafts must be occluded)
- v. Left ventricular ejection fraction >20%
- vi. Require at least one SVG as part of revascularization strategy
- vii. eGFR of at least 30 mL/min or higher

## **4.2 Exclusion Criteria**

- i. Unable to use greater SV due to previous vein stripping or poor quality on mandatory preoperative Duplex study and vein mapping
- ii. Contraindication to receiving follow-up 64-slice cardiac CT angiography (allergy to contrast dye, renal failure with a creatinine >180 µmol/L, uncontrolled atrial fibrillation precluding proper gating of study)
- iii. Pregnant women, or women of child-bearing age
- iv. Allergy to fish oil/fish products, and non-medicinal ingredients of the study product (corn oil, soybean oil, gelatine, glycerol, or carob colouring)
- v. Already taking fish oil supplements regularly (daily use in the past 30 days)
- vi. Congenital or acquired coagulation disorders
- vii. Patients considered to be of excessive risk of wound infection according to the **clinical judgment of the site surgical investigator**. N.B. Patients that are excluded for anticipated excessive risk of wound infection need to have the reasons for exclusion well documented in the screening log. We expect that the excluded patients will have advanced comorbidities or multiple risk factors for wound infection (such as peripheral vascular disease, peripheral edema, diabetes mellitus, obesity, advanced age, malnutrition, steroid dependence, concurrent infection, concurrent malignancy, or frailty).

## **5 STUDY PROCEDURES**

### **5.1 Treatments**

#### **A. SURGICAL ARM**

Eligible patients undergoing multi-vessel CABG with ≥1 SVG, will have the study SVG directed to the most important coronary target intended for a venous conduit. **In the experimental arm**, patients will be randomized to have the study SVG harvested from their lower leg using the novel, pedicled, atraumatic **“no touch” technique** (45-48). **In the control group**, patients will have their study SVG graft harvested in a **conventional fashion** without a pedicle.

The atraumatic “no touch” approach involves a longitudinal incision in the lower leg below the knee to the medial malleolus. However, the SVG is harvested with its surrounding tissue (pedicled). It is not manually dilated; it is left *in situ* until required and allowed to dilate when exposed to arterial pressure. All study patients will undergo duplex scanning and mapping of the saphenous veins preoperatively, to assess the quality of the vein as well as limit the creation of flaps during the vein dissection. Saphenous veins will be harvested from the thigh in the event that the lower leg vein is of poor quality or small size, or in patients with marked edema or peripheral vascular disease with concerns regarding wound healing.

The conventional approach involves a longitudinal incision in the lower leg, just below the knee to the medial malleolus. The vein is identified and the adventitial layer is stripped to directly expose and visualize the SV and its branches. Vein from the thigh may be harvested for similar reasons as

discussed above. It is then excised and distended using heparinized saline. It is standard practice in many institutions to harvest SV using an endoscopic, minimally invasive rather than an open approach, for reasons of improved cosmesis and because local wound complications are reduced (70). For relevance and to reflect contemporary trends in practice, the control group/conventional approach may include the minimally harvested SVG, which is otherwise prepared in a similar manner, i.e. stripped of adventitia and manually distended, albeit through a smaller incision. A recent observational study of a large multi-centre sample (50) and post hoc secondary analysis from the large multi-centre PREVENT IV RCT (5) reported poorer patency and clinical outcomes using endoscopically harvested SVG, however, institutions that predominantly employ endoscopic harvesting may continue to choose this technique.

All patients will have their left anterior descending coronary artery grafted with an internal thoracic artery, the standard of care for CABG. The study SVG, directed to the most important target intended for a venous conduit, may be to the second, third or fourth territory chosen; this design allows for the use of multiple arterial grafting as per surgeon discretion/patient indication. The surgeon will identify the proposed target for the study graft prior to surgery. While the site of SVG harvesting (right or left leg) and the coronary target grafted (circumflex, right coronary, or branch [i.e. diagonal]) will not be randomized, all site and target vessel characteristics will be recorded for post-hoc multivariable regression analysis. Surgeons will be encouraged to use the study SVG for a single distal target. If a sequential graft is required, it will only be considered patent at follow-up angiography if it is entirely patent to all sequentially grafted targets. If more than one SVG is used, surgeons will also be encouraged to harvest all SVGs using the same technique (either all “no touch” or all conventional). While this decision will not impact the primary outcome of ‘study graft’ patency between the two groups (i.e. the SVG directed to the most important vein graft target), it may increase the ability to detect differences in clinical outcomes at 1-year.

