### **3 STUDY DESIGN**

#### **3.1 Type of study**

This study is an International, multi-centre, prospective, controlled RCT using a 2x2 factorial design; involving a surgical intervention and a pharmacological intervention. For the surgical intervention, surgeons will be unblinded while patients, care providers, data collectors and outcome adjudicators will be blinded. For the pharmacologic intervention, patients, all care providers, data collectors and outcome adjudicators will be blinded. Approximately 10 Canadian and 40 International centers will participate.

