### **3.3 Method of treatment allocation**

Prior to the trial, all surgeons will be provided with a copy of the trial protocol. Research personnel will screen patients in the preoperative assessment clinic to identify patients who fulfill the eligibility criteria. The personnel will also review the daily surgical list for eligible in-patients. Patients who fulfill the eligibility criteria will be approached for informed consent. Eligible and consenting patients will be randomized by calling a 24 hour interactive voice response system (IVRS) or by logging-in to a web-based randomization service. Treatment allocation to either “no touch” or conventional SVG harvesting, and fish-oil supplementation or placebo will be performed according to a computer generated randomization list. This will be stratified by site using a factorial design; blocked randomization will be performed with randomly sized blocks to maintain concealment. Randomization will also be stratified according to the control technique (open vs. endoscopic) to minimize bias following the pilot phase. Patients will be considered as randomized as soon as the treatment allocation is given over the telephone.

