## **B. PHARMACOLOGICAL ARM**

Patients will be randomized to receive either fish-oil oral supplements (Ocean Nutrition, Dartmouth, NS) or a colour and taste-matched placebo (Ocean Nutrition, Dartmouth, NS). Upon randomization at the time of accepting referral for surgery and consent, the subjects will consume two 1g tablets, daily (as used in prior clinical trials) for 1 year. Study supplements will not be administered on the day of surgery. The duration of preoperative therapy is not mandated but will be evaluated post hoc; surgery should occur within 30 days of randomization. In the event that the patient misses any dose(s) of study supplement, patients will be instructed to resume the next scheduled study dose and discouraged from taking more than two study supplements per day.

Postoperative medical management using aspirin and/or other antithrombotic agents, statins, beta blockers and/or ACE-inhibitors will be prescribed in a standardized fashion according to published STS and AHA/ACC guidelines.

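### The protocol does not require the study-graft target to be recorded before the allocation is released, so an unblinded surgeon may name the graft that defines the surgical primary endpoint knowing the arm

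*Protocol*

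**What the plan says.** **Choice of the study graft.** Section 5.1 A says that patients "will have the study SVG directed to the most important coronary target intended for a venous conduit". It then says: "The surgeon will identify the proposed target for the study graft prior to surgery". The coronary target is not randomized. Its characteristics are recorded for post-hoc regression. On the split between arterial and venous conduits, the same section says that "this design allows for the use of multiple arterial grafting as per surgeon discretion/patient indication".

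**Allocation.** Section 3.3: "Treatment allocation to either “no touch” or conventional SVG harvesting, and fish-oil supplementation or placebo will be performed according to a computer generated randomization list". It adds: "Patients will be considered as randomized as soon as the treatment allocation is given over the telephone". Section 5.1 B places this event early ("Upon randomization at the time of accepting referral for surgery and consent") and says that "surgery should occur within 30 days of randomization".

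**Blinding.** Section 3.1: "For the surgical intervention, surgeons will be unblinded while patients, care providers, data collectors and outcome adjudicators will be blinded".

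**Endpoint.** In Section 5.5 the surgical primary outcome is total occlusion of the study SVG at 1 year, together with death from cardiovascular or unknown causes. Section 8.3 tests it with an unadjusted chi-square test.

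**The concern.** One graft per patient carries the surgical comparison. If that graft is designated after the arm is known, randomization balances the patients but no longer guarantees that the designated grafts are comparable. Section 8.3 lists the size and quality of the distal target and the severity of the proximal stenosis among its variables of interest for graft occlusion, so the protocol itself treats the choice of target as relevant to outcome.

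No deliberate steering is needed. Section 1.B.IV notes that the no-touch harvest may take longer, and a practical difference of that kind could influence which vessel receives the study vein.

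The later safeguards act on other steps. Random block sizes conceal the next assignment, blinded adjudication protects the reading of the graft, and intention-to-treat keeps patients in their arm. None of them fixes which graft is read.

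**Working it through.** **1. Order of events in the protocol**

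| Step | Timing stated | Source |
|---|---|---|
| Consent, randomization, allocation issued | At acceptance of referral | Sections 3.3, 5.1 B |
| Baseline CRF | Soon after randomization | Section 5.3 |
| Target of study graft named | Before surgery | Section 5.1 A |
| Surgery | Up to 30 days after randomization | Section 5.1 B |
| Surgical details recorded | Day of operation | Table 1 |

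The target may be named at any time up to surgery. Even a target written on the baseline form could postdate the allocation. Table 1 has no preoperative item for the target. The protocol therefore creates no record that would show the choice was made independently of the arm.

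**2. The plan's own figure**

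Inputs from Section 8.5 A: 20% versus 14% occlusion, two-sided alpha 0.05, power 80%. With pooled variance under the null and a mean rate of 17%:

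n = [1.96·√(2·0.17·0.83) + 0.842·√(0.20·0.80 + 0.14·0.86)]² / 0.06² = 614.1, rounded up to 615 per group.

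615 / 0.80 = 768.75, or 769 per group and 1,538 in total, which the protocol rounds to 1,550. The figures reproduce and are not in dispute.

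**3. Illustration of size**

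Section 5.4 expects 1.5 vein grafts per patient. The other inputs are assumptions that the protocol does not give:
- half of patients have one vein graft and half have two;
- the occlusion risk differs by 6 to 12 points between the better and the worse vein target;
- in 10% to 30% of the two-graft patients, net and in one direction, the nomination differs by arm.

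Spurious difference = 0.5 × share nominated differently × occlusion gap:
- low: 0.5 × 0.10 × 6 = 0.3 points
- middle: 0.5 × 0.20 × 9 = 0.9 points
- high: 0.5 × 0.30 × 12 = 1.8 points

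With 615 per group and a 17% base rate, SE = √(2 × 0.17 × 0.83 / 615) = 2.14 points. With no true effect, the chance of a significant result in the favoured direction is P(Z > 1.96 − shift/SE):

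| Shift | Shift/SE | False positive in that direction (nominal 2.5%) | Share of planned 6 points |
|---|---|---|---|
| 0.3 | 0.14 | 3.4% | 5% |
| 0.9 | 0.42 | 6.2% | 15% |
| 1.8 | 0.84 | 13.1% | 30% |

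At a 20% base rate the SE is 2.28 points, and the low and high results become 3.4% and 12.1%.

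If the shift ran against no-touch, it would cost power instead. For a true 20% versus 14%, power falls from 80% to 64% at a 1-point shift and 45% at 2 points.

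The calculation leaves out patients with a single vein graft. The surgeon's discretion over the arterial and venous plan could also change which vessel gets that vein, but the protocol gives no basis for sizing this.

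**The case against.** A reader might infer that the surgeon already knows the allocation when naming the target. The protocol does not say so. Naming it before surgery is compatible with naming it before randomization. Research personnel screen and approach the patients, and nothing states when the surgeon is told the arm. What is established is an order left open, not a breach built into the design. This objection stands.

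Other constraints also count. The rule that the study SVG goes to the most important vein target is the same in both arms, and picking an easier vessel for one arm would violate it. Eligibility requires at least one SVG in the revascularization strategy, so some conduit plan exists before randomization. Target characteristics are recorded for every patient, so an imbalance in what is recorded could be seen.

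These points narrow the gap without closing it. Importance has no stated criterion, and which vessels are intended for a vein is itself discretionary. The recorded characteristics enter only post-hoc models, which cannot correct for features of the target that were not recorded.

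The illustration is open to fair challenge as well. Its gap and its share are assumed, it needs a net shift in one direction across about 50 centres, and its low end is negligible.

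**Conclusion.** The point holds as a gap in sequence: the protocol permits the graft that defines the surgical primary endpoint to be named with knowledge of the arm, and it provides no record to show otherwise. The documents do not support saying that this will happen, or that the randomized comparison is broken.

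The size and direction of any bias are unknown. Under the assumptions stated above, the spurious difference is 0.3 to 1.8 points against a planned 6, and the one-direction false-positive rate is about 3.4% to 13% against 2.5%. The upper figure is the worst corner of the assumed range and should not be quoted alone.

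Only the surgical primary endpoint is exposed. The pharmacological one counts an occlusion in any graft. The reason to act is that the remedy is nearly free, while a missing pre-allocation record cannot be recreated once patients are randomized.

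**What to change.** Amend Section 5.1 A, and Section 3.3 to match:

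- The proposed study-graft target is entered in the IVRS or web system before the allocation is released.
- The study SVG for the primary analysis is designated from that entry.
- Every intraoperative change of target or conduit is logged with its reason, and changes are reported by arm.
- The protocol states in advance how patients are counted when the declared target receives no vein graft, since the occlusion endpoint would otherwise be undefined for them.

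The cost is one mandatory field and one rule for intraoperative changes. The sample size (615 evaluable, 769 randomized per surgical group) is unchanged, and the surgeon's operative freedom is untouched.

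Two further steps are not needed. A separate field for the intended control technique adds little, because Section 3.3 already stratifies by open versus endoscopic harvest after the pilot. Withholding the harvest technique until the day of surgery is debatable and could affect scheduling, and recording the target first already closes the gap.

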## **B. PHARMACOLOGICAL ARM**

Patients will be randomized to receive either fish-oil oral supplements (Ocean Nutrition, Dartmouth, NS) or a colour and taste-matched placebo (Ocean Nutrition, Dartmouth, NS). Upon randomization at the time of accepting referral for surgery and consent, the subjects will consume two 1g tablets, daily (as used in prior clinical trials) for 1 year. Study supplements will not be administered on the day of surgery. The duration of preoperative therapy is not mandated but will be evaluated post hoc; surgery should occur within 30 days of randomization. In the event that the patient misses any dose(s) of study supplement, patients will be instructed to resume the next scheduled study dose and discouraged from taking more than two study supplements per day.

Postoperative medical management using aspirin and/or other antithrombotic agents, statins, beta blockers and/or ACE-inhibitors will be prescribed in a standardized fashion according to published STS and AHA/ACC guidelines.

## **5.2 Schedule of visits and observations**

Study subjects will have clinical assessments preoperatively, pre-discharge, 1-month, 3-month, 6-month, 9-month, and 1-year postoperatively (see Table 1 and Figure 1). The preoperative visit will consist of an evaluation of eligibility criteria, obtaining informed consent, gathering demographical, medical history, blood work and ECG information. Fish oil supplementation or placebo will be

**CONFIDENTIAL**  
SUPERIOR SVG – 2011-06-13

commenced at this visit. Study supplements will not be administered on the day of surgery. Blood will be drawn at induction for the preoperative CK-MB (5 mL draw for preoperative CK-MB). The discharge visit will consist of a patient evaluation and blood work (5 mL draw for 24 hour post-operative CK-MB). At this time, a 3-month supply of the fish oil supplement or placebo will be given (by the Site Study Nurse). The 30-day visit will consist of a patient evaluation, assessment of leg wound, and a drug compliance check. The 3-month visit will consist of a patient evaluation, assessment of leg wound, and drug compliance check. The 6-month and 9-month visits will consist of a patient evaluation and drug compliance check. At the 3-month, 6-month and 9-months visits, a 3-month supply of the fish oil supplement or placebo will be given. The 1-year visit will consist of a patient evaluation, blood work (5 mL draw for serum creatinine), assessment of leg wound, drug compliance check, and cardiac CT angiography (acceptable window for angiography is 9-15 months postoperatively). ECG and blood work (creatinine) information will also be collected at this time as the patient will need to have these tests done prior to undergoing the CCTA. Patients with an estimated GFR < 30 mL/min will not be eligible for the study CT angiography. Patients with an estimated GFR of 30-60 mL/min may undergo the study CT angiography with renal precautions according to the institutional protocol, which may include any or all of the following: saline hydration, sodium bicarbonate loading, n-acetyl cysteine prophylaxis, and temporary stoppage of potentially nephrotoxic drugs and metformin.

**Table 1:** Schedule of follow-up

| VISIT SCHEDULE                  | Pre-op  | OR Day | Discharge | 30 Day | 3 Mth | 6 Mth | 9 Mth | 1 Year |
|----------------------------------------|----------------|---------------|------------------|---------------|--------------|--------------|--------------|---------------|
| Evaluation of Inclusion Criteria       | ✓              |               |                  |               |              |              |              |               |
| Informed Consent                       | ✓              |               |                  |               |              |              |              |               |
| Demographics                           | ✓              |               |                  |               |              |              |              |               |
| Blood Work (creatinine)                | ✓              |               | ✓ a   |               |              |              |              | ✓             |
| Blood Work (CK-MB)                     | ✓              |               | ✓ b   |               |              |              |              |               |
| Medical History                        | ✓              |               |                  |               |              |              |              |               |
| Start Fish Oil Supplementation/Placebo | ✓ c |               |                  |               |              |              |              |               |
| Details of Surgical Procedure          |                | ✓             |                  |               |              |              |              |               |
| Patient Evaluation                     | ✓              |               | ✓                | ✓             | ✓            | ✓            | ✓            | ✓             |
| Clinical Outcomes                      |                |               | ✓                | ✓             | ✓            | ✓            | ✓            | ✓             |
| Leg Wound Assessment                   |                |               |                  | ✓             | ✓            |              |              | ✓             |
| Refills Given of Supplement/Placebo    |                |               | ✓                |               | ✓            | ✓            | ✓            |               |
| Supplement Compliance Checks           |                |               |                  | ✓             | ✓            | ✓            | ✓            | ✓             |
| ECG                                    | ✓              |               | ✓ d   |               |              |              |              | ✓             |
| Quality of Life Questionnaire          | ✓              |               |                  | ✓             |              |              |              | ✓             |
| Cardiac CT Angiography                 |                |               |                  |               |              |              |              | ✓             |

a Highest serum creatinine value within seven days post surgery and last serum creatinine value prior to hospital discharge

b CK-MB at 24-hours postoperatively

c Study supplements not to be administered on day of surgery

d ECG 24-hours postoperatively and within 4-7 days postoperatively

[figure not shown]

**Figure 1:** Flow chart of scheduled patient visits

